#### Occupational therapist intervention

The occupational therapist affiliated with the study will be asked to consult the participants who suffer from eating dependency or chewing and swallowing problems according to the EVS. The task of the occupational therapist is to determine if the participant actually has swallowing or chewing problems, or if any help during meals is needed, and initiate intervention to solve these problems.

Specifically, the initial dysphagia assessment will consist of indirect and a direct swallowing tests. Indirect swallowing test assess the ability to be awake and alert, sit up, have control of the head, coughing and clear throat at request, swallowing own saliva and have a clear voice. Direct swallowing test consist of 3 steps. Step one: swallowing 3× teaspoon of water. Step two: Drinking 50 ml of a glass of water. Step three: observation during a meal (based on
[20, 21]). There will be follow-up as needed, in participant’s home, in connection with the group exercise or by telephone. In addition, contact with be made to caregivers, food service supplier, dental hygienist, the visitation for the referral of eating aids and others where appropriate. The time used for the initial assessment and follow-up will be documented.

#### Compliance with intervention strategies

The physiotherapists will document the consumption of ONS (recorded as 1, ¾, ½, or ¼ portion consumed).

After each exercise bout, the physiotherapist will record each participant’s attendance, training intensity, and potential adverse events. The registered dietician and occupational therapist will document number of visits, reasons for cancelling appointments and possible problems with the suggested intervention strategies.

### Procedure for baseline assessment

After obtaining participants’ informed consent an inventory will be made of possible confounders. This includes the following baseline characteristics:Socio-demographic data (age, gender, living conditions, i.e. in a nursing home or in own home)Social services, i.e. hours and type of home help and home nursing (for home-care clients) from the municipality care register system.Functional, nutritional, medical, cognitive, psychological and social status by means of the Resident Assessment Instrument (RAI) for, respectively home-care (RAI-HC version 2.0) and nursing home (RAI-NH version 2.0). RAI is a comprehensive and standardized assessments system. Each item of the RAI has its own explicit definition and coding conventions, and a manual developed for the 2.0 versions describes how to ask questions, what to observe, and whom to contact for information. Both RAI-NH and RAI-HC has been translated into Danish (and several other languages). Studies have shown that inter-rater reliabilities for respectively the RAI-NH version 2.0 and RAI-HC version 2.0 items are adequate for research purposes, and both methods have been used in former Danish studies (see e.g. [5, 12]).

Trained nurses involved in the former studies above and affiliated with the present study will assess participant’s performance. All collected information will be discussed and crosschecked with the attending care givers and medical records. These data will also be collected at the end of the intervention period (see outcome parameters below).

### Outcome parameters

We will compare changes in quality of life, physical performance, nutritional status, oral care, fall incidents, hospital admissions, rehabilitation stay, moving to nursing homes (for home-care participants), use of social services and mortality between the intervention and control group.

All outcome parameters will be measured after inclusion (t = 0) and after 11 weeks (t = 11). In addition, the intervention group will have their weight measured approximately once a week. Primary outcome is health-related quality of life determined as EuroQol-5D-3L. If nothing else is stated data is gathered by the research assistants or the caregivers. All outcome parameters that will be measured are listed below.

#### Quality of life by means of EuroQol-5D-3L (t = 0 and t = 11)

EuroQol-5D-3L (EQ-5D-3L) is a standardized instrument for use as a measure of health outcome. The EQ-5D-3L descriptive system comprises the following 5 dimensions (5D): mobility, self-care, usual activities, pain/discomfort and anxiety/depression. Data will be collected by nurses affiliated with the study.

Each dimension has 3 levels (3L): no problems, some problems, extreme problems. The raw score must be converted to an EQ-5D-3L score ranging from 1.000 to -0.624
[22]. The EQ-5D-3L scores will be used to calculate utilities using the Danish tariff
[23].

#### Physical performance by means of 30 seconds chair-stand (t = 0 and t = 11)

Participants are asked to fold their arms across their chest and to stand up and sit down on a chair without pushing off with arms, as many times as possible during 30 seconds. The arms may be used for assistance or for safety if need
[24]. The mode of chair stand will be registered.

#### Nutritional status by means of weight, height, BMI and hand-grip strength (t = 0 and t = 11)

Weight (in kg to the nearest decimal) is measured (with participants wearing light indoor clothes, i.e. night dress) on calibrated weights present in the different settings. In addition, the participants in the intervention group will be weighed once a week before the start of the exercise and/or in relation to the registered dietician consultations. As measurement of height is often not feasible in this old and frail population with chronic disease, data about height will be retrieved from self-reported height. BMI is calculated as actual weight in kilograms divided by the square of height in meters.

Hand-grip strength will be measured (in kg) with a Jamar 5030J1 Hydraulic Hand Dynanometer. Participants will be seated with forearms rested on the arms of the chair. They are asked to perform three maximum force trials with their dominant hand and using the second handle position. The maximal grip score from the three values will be used.

#### Oral care by means of RAI-NH, RAI-HC and observation (t = 0 and t = 11)

The RAI-NH version 2.0 and RAI-HC version 2.0 contain information about oral care. These data will be supplied by grading the hygienic level based on three pictures of dental plaque: no plaque, plaque covers less than half of the tooth surface, and plaque covers more than half of the tooth surface.

Pictures are provided from a public dental health care program in the municipality of Aarhus.

#### Fall incidents, hospital admissions, rehabilitation stay, moving to nursing homes, and mortality (t = 11)

These information’s will be gathered by means of data from the RAI-NH version 2.0 and RAI-HC version 2.0 assessments and the municipality care register system.

For each participant the same trained nurse will collect RAI-NH version 2.0 and RAI-HC version 2.0 data at t = 0 and t = 11.

#### Economic evaluation (t = 11)

At the end of the trial, having received the data, an economic evaluation of the intervention will be carried out. This evaluation will take the form of a cost-effectiveness study, in which the intervention with its different forms of nutritional support is modeled as a decision tree, so that the citizen is followed through the intervention, costs and effects being assigned to its different varieties.

The effects of the intervention will be measured both in terms of changed body weight and as change in health-related quality of life, measured in QALYs on the basis of the EQ-5D-3L measurements. Time used for the different tasks will be registered and used in the calculations. The cost of the intervention includes cost of screening, cost of the multidisciplinary nutritional support and cost of training the staff for the specific tasks specified by the intervention. The results will be compared to other interventions in healthcare, and the uncertainties in the assessments will be illustrated by suitable sensitivity analyses.

#### Interviews (t = 0 and t = 11)

Before the intervention managers and selected staff members of the participating nursing homes and home-care districts will be interviewed on their attention to the nutritional state of the citizens, practice with respect to screening for nutritional problems, nutritional support, division of responsibilities and tasks, and inhibitory and promoting factors for nutritional support. At the end of the intervention managers and selected staff will be re-interviewed on the same issues as to assess whether practice has changed in the intervention clusters and the control clusters.

At the end of the intervention the multidisciplinary team will be interviewed on their performance of the intervention, the collaboration within the team, and the collaboration with nursing-home staff and home-care staff.

At the end of the intervention a selected small number of participants of the intervention will be interviewed on their expected benefits from participating, experienced benefits, and their assessment of the intervention.

### Statistical analysis

All statistical analysis will be performed using SPSS for Windows. Data will be entered in EXCEL and will subsequently be exported into SPSS software for analysis. Data will be analyzed by the Primary Investigator who is blinded for the results of randomization. All participants will be included in the analysis, regardless of whether they have completed the study or not. Depending on the data type and distribution t-test, Mann-Whitney U test and Chi2 test will be used to compare changes within and between the groups.

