## Methods

### Design

This study is designed as an 11 week cluster randomized controlled trial assessing the benefits of a new model for multidisciplinary nutritional support. The protocol has been send to the Danish Ethical Board which has concluded that approval is not needed and that the project can be carried on as described.

Older adults are eligible for this study when they are 65+ years old and achieve 2 points in the EVS (see below)
[10].

The primary outcome parameter will be change in quality of life (by means of Euroquol-5D-3L, see below). Secondary outcomes will be: physical performance (chair stand), nutritional status (weight, BMI and hand-grip strength), oral care, fall incidents, hospital admissions, rehabilitation stay, moving to nursing homes (for participants from home-care), use of social services and mortality.

An economic evaluation will be conducted alongside the randomized trial to evaluate the cost-effectiveness of the multidisciplinary support.

Furthermore, interviews with nursing home and home-care management, nursing staff and nutrition coordinators in both the control and intervention groups, participants in the intervention group and the involved multidisciplinary team will be performed.

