### Feasibility of recruitment and sample size

Unpublished results have shown that around 25% of nursing home residents will achieve 2 points in the EVS. According to our knowledge no nutritional support studies among nursing home residents and home-care clients have used Euroquol-5D-3L. However in a study of multidisciplinary nutritional support among another frail group of older adults, patients with hip fractures, Hoekstra and co-workers
[15] used this measure and found a significant difference between intervention and control group in the Euroquol-5D-3L follow-up score of 0.145 (p = 0.004). Hence, with a statistical significance level of 0.05 and a power of 80% two groups of 65 older adults is calculated to be sufficient. The above mentioned unpublished study found that it was possible to screen 600 nursing home residents during an 8 weeks period.

Taking into account an expected loss to follow up of 10% during the 11 weeks of intervention based on a former multidisciplinary study among nursing home residents
[12], and estimating equal findings among home-care clients, we aim to include a total of 145 older adults with 2 points in EVS. We therefore need to screen about 600. This number could probably be reached in approximately 8 weeks.

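### Mann-Whitney U and Chi2 are assigned to within-group change as well, although both assume independent samples and the t = 0 and t = 11 data are paired (minor)

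*Protocol article*

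**What the plan says.** The Statistical analysis section gives one list of tests for two purposes: "Depending on the data type and distribution t-test, Mann-Whitney U test and Chi2 test will be used to compare changes within and between the groups". The choice among them depends only on data type and distribution. The section does not say whether the t-test is paired, and it names neither the Wilcoxon signed-rank test nor the McNemar test.

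The Outcome parameters section makes the data paired: "All outcome parameters will be measured after inclusion (t = 0) and after 11 weeks (t = 11". The headings for quality of life, chair stand, nutritional status and oral care each repeat both time points. For the RAI data the plan adds: "For each participant the same trained nurse will collect RAI-NH version 2.0 and RAI-HC version 2.0 data at t = 0 and t = 11". The heading for falls, admissions, rehabilitation stay, moves and mortality gives t = 11 only.

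The main contrast is between groups. The Design section states: "The primary outcome parameter will be change in quality of life (by means of Euroquol-5D-3L, see below". The Outcome parameters section lists the outcomes whose changes are compared, ending with "use of social services and mortality between the intervention and control group".

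**The concern.** A within-group change compares two measurements on the same person. Mann-Whitney U and Pearson Chi2 derive their standard error from two unrelated samples, and neither has a paired form. Of the three tests listed, only the t-test can be read as paired. Under the stated rule, an outcome judged non-normal or categorical is therefore left without a suitable within-group test. Candidates are the chair-stand count, the three-level plaque grade, the RAI oral-care items and, depending on its distribution, EQ-5D-3L.

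At stake is the reporting of change within each group: a real change could be given a p-value that is too large and be described as absent.

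**Working it through.** **The plan's own figure.** The Feasibility of recruitment and sample size section uses a difference in "Euroquol-5D-3L follow-up score of 0.145 (p = 0.004" and concludes that "with a statistical significance level of 0.05 and a power of 80% two groups of 65 older adults is calculated to be sufficient". No SD is given, so it is solved backwards, taking the test as two-sided:

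SD = 0.145 × √(65/2) / (1.96 + 0.8416) = 0.295.

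With SD 0.295 the two-sample formula returns 65 per group at 80% power. Inflating for 10% loss gives 130 / 0.90 = 144.4, rounded up to 145, as stated. All of this concerns the between-group difference; nothing in it depends on the within-group tests.

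**Why the error has a direction.** For n people measured twice, with common SD σ and correlation ρ, the difference between the two means has variance 2σ²(1 − ρ)/n. An independent-sample test uses 2σ²/n. With no true change, its statistic therefore has SD √(1 − ρ) instead of 1, and a nominal 5% two-sided test has true level

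α = 2 × [1 − Φ(1.96 / √(1 − ρ))].

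- ρ = 0: 1.96 / 1 = 1.96, α = 0.050
- ρ = 0.3: 1.96 / 0.837 = 2.34, α = 0.019
- ρ = 0.5: 1.96 / 0.707 = 2.77, α = 0.006
- ρ = 0.7: 1.96 / 0.548 = 3.58, α = 0.0003

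**Simulation for the tests named.** The inputs are 65 pairs (from the plan), SD 0.295 (implied above), bivariate normal scores, and ρ (assumed; the documents give none). There were 20,000 runs, 5,000 for signed-rank. Binary data are the same scores cut at the baseline median, so ρ there is the correlation before the cut. Chi2 compares the t = 0 and t = 11 proportions as two samples.

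Rejection rate with no true change, nominal 5%:

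| ρ | Mann-Whitney | Signed-rank | Chi2 | McNemar |
|---|---|---|---|---|
| 0 | 0.049 | 0.047 | 0.042 | 0.050 |
| 0.3 | 0.022 | 0.043 | 0.025 | 0.053 |
| 0.5 | 0.007 | 0.048 | 0.015 | 0.051 |
| 0.7 | 0.0006 | 0.053 | 0.005 | 0.047 |

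Power for a within-group shift of 0.0725 (half of 0.145, chosen for illustration) and of 0.145:

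| ρ | Mann-Whitney, 0.0725 | Signed-rank, 0.0725 | Mann-Whitney, 0.145 | Signed-rank, 0.145 |
|---|---|---|---|---|
| 0 | 0.28 | 0.28 | 0.78 | 0.79 |
| 0.3 | 0.23 | 0.36 | 0.81 | 0.90 |
| 0.5 | 0.20 | 0.49 | 0.85 | 0.97 |
| 0.7 | 0.15 | 0.69 | 0.91 | 1.00 |

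For binary items at the 0.0725 shift, Chi2 against McNemar gives 0.16 against 0.24 (ρ = 0.3), 0.14 against 0.28 (ρ = 0.5) and 0.11 against 0.34 (ρ = 0.7).

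**The case against.** The strongest defence is that this is one condensed sentence in a journal article, naming families of tests for two purposes. It does not say whether the t-test is paired, so it may simply not be specific at that level, and the paired variants could be in a fuller plan that is not shown. This stands in part: what the analysts will actually run is not certain. It does not remove the point, because the sentence explicitly assigns the named tests to within-group change, and two of the three do not fit that purpose.

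The second defence is that no main conclusion depends on it. This stands in full. For the between-group contrast, an independent-sample test on change scores is the right type of test, clustering aside.

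Three stronger readings are tempting, and the document does not support them:

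- A reader might infer that the tests address the wrong null. Mann-Whitney, and Chi2 on the two sets of proportions, do compare the t = 0 and t = 11 distributions. The fault is the independence assumption, and hence the variance.
- A reader might infer false claims of change, for example from a Chi2 on the t = 0 by t = 11 cross-table, which tests association. Nothing in the section proposes that analysis. With the two time points treated as two samples and a positive correlation, the error is conservative.
- A reader might infer that every outcome is affected. A paired t-test may be intended for continuous outcomes, and the outcomes headed t = 11 only are outside this point.

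**Conclusion.** The point holds as a minor fault of specification. Applied as written to within-group change, Mann-Whitney U and Chi2 give p-values that are too large for non-normal and categorical outcomes when the two measurements on a person are positively correlated. For Mann-Whitney at 65 per group, the true level falls from 5% to about 2% at a correlation of 0.3, 0.7% at 0.5 and 0.1% at 0.7. Power for a shift of 0.0725 falls from 0.36 to 0.23, from 0.49 to 0.20 and from 0.69 to 0.15 respectively. At zero correlation the loss disappears.

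The size rests on assumptions: the correlation and the shift are not in the documents, the SD is only implied by the sample size, and the simulated scores are normal. The simulation also treats participants as independent of one another. Signed-rank and McNemar make that assumption too, so their 5% level holds only without clustering.

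**What to change.** In the Statistical analysis section, name paired methods for within-group change: the paired t-test for continuous outcomes, the Wilcoxon signed-rank test for non-normal or ordinal outcomes such as chair stand and plaque grade, and McNemar for binary items. Label these results descriptive and state that conclusions rest on the between-group contrast.

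The new wording should not read as approval of the listed tests for the between-group comparison. Those tests ignore the six randomized clusters, a separate and weightier issue that this change leaves open.

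The cost is a sentence or two. The paired tests are available in SPSS, which the plan already uses, and no new data are needed.

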### Nutritional status

Participants are eligible for this study if they are identified with 2 points according to EVS
[9]. EVS contains information about eating habits, recent unintended weight loss, and the presence or absence of potentially modifiable nutritional risk factors (eating dependency, chewing and swallowing problems, acute disease, or acute change in chronic disease). The information is combined to give a total number of points, 0 point (no risk), 1 point (at risk), and 2 points (intervention).

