### Control group

Before start of the intervention a nutrition education program will be performed educating selected staff members from the participating home-care and nursing homes to take the role as nutrition coordinator. The education of the nutrition coordinator includes three whole-day courses plus train-the-trainer sessions with other staff members (based on
[13]) and local study circles in-between (based on
[17]). These nutrition coordinators will be active in both the control and the intervention group. Also, in both groups standard interventions from physiotherapist, registered dietician and occupational therapist requested through the municipality’s normal assessment and referral system will be maintained.

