### Weaknesses

We have chosen to include participants with 2 points in EVS, instead of using e.g. the Mini Nutritional Assessment (MNA), which might limit the comparability with other studies. The reason for choosing EVS is that this tool, in contrast to e.g. the MNA is developed and validated in order to identify older adults in home-care and nursing home, who could benefit from nutritional support. However, whether this is actually true has never been examined before
[10].

The participants included in the study should be able to complete the planned tests and to give informed consent. These criteria might exclude demented and functionally impaired persons and hence reduce the representativeness of our findings.

Furthermore, according to our knowledge, there have only been performed a few randomized controlled studies of nutritional support among home-care clients and none using a multidisciplinary approach.

Finally the EQ-5D-3L has apparently not been used in this population before. Hence our expectations about feasibility of recruitment and sample size assessment are based on relatively few published data, primarily among nursing home residents. However we expect that the home-care population is less frail than the nursing home population and therefore may be more willing to participate.

In relation to this, we have decided to use cluster randomization to avoid contamination. Hence the estimated sample may be too small to detect a significant difference
[25]. Due to limited time and resources it is not possible to increase the number of clusters. To try to compensate for this we aim to include statistical analysis of the percentage of individuals in the different clusters that benefits.

We could have decided to use the Short Physical Performance Battery (SPPB) for the functional assessment. SPPB measures chair rise, balance and gait speed. However instead we decided to use methods which we had experience working with from former studies, and which gives some of the same information as the SPPB, i.e. 30 seconds chair-stand and RAI.

We have decided to use quality of life as our primary outcome. Another relevant outcome measure could have been ADL, especially since former studies have shown that older adults in respectively, nursing homes and home-care, who are undernourished, need more assistance with ADL than older adults who are in good nutritional status and due to that, may add to the substantial and costly burden of care

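### The analysis section plans tests of change within each arm without giving them a role; they cannot isolate the support's effect, and two of the three named tests do not suit paired data

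*Protocol article*

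**What the plan says.** The Statistical analysis section names three tests for two purposes in one sentence: "t-test, Mann-Whitney U test and Chi2 test will be used to compare changes within and between the groups". It ranks neither purpose above the other and does not say what the within-group tests are for.

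Elsewhere the article treats the question as one between arms. The outcome section ends its list of changes to be compared with "use of social services and mortality between the intervention and control group". The sample size in Feasibility of recruitment and sample size rests on a between-group EQ-5D-3L difference of 0.145.

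Two features bear on what a within-arm change contains:

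- **Entry.** The Nutritional status section says "Participants are eligible for this study if they are identified with 2 points according to EVS", which is the highest category. The score uses recent unintended weight loss and the risk factors "eating dependency, chewing and swallowing problems, acute disease, or acute change in chronic disease".
- **Shared background care.** The Control group section says "Before start of the intervention a nutrition education program will be performed educating selected staff members", and then "These nutrition coordinators will be active in both the control and the intervention group".

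**The concern.** The trial asks what the multidisciplinary support adds to coordinators plus ordinary referral. Only the contrast between randomised arms answers that. A before-after test in the intervention arm adds together three things: the course participants would have followed anyway, whatever the coordinators achieve during the 11 weeks, and the support itself.

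The misreading can go either way. If the untreated course is upward, a significant gain in the intervention arm beside a non-significant one in the control arm invites a claim of benefit when the arms do not differ. If the untreated course is downward, support that slows the decline shows up within the arm as no improvement.

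The risk is practical. The Weaknesses section concedes that the sample may be too small to show a difference under cluster randomisation, and the Strengths section says positive results would justify broad adoption by municipalities. A null between-arm result printed next to a significant within-arm p-value could easily be over-read.

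There is also a plain technical fault. Mann-Whitney U and the ordinary Chi2 test assume independent samples, whereas measurements on the same person at t = 0 and t = 11 are paired. Of the three named tests, only the t-test has a paired form under the same name.

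**Working it through.** **Inputs from the article:** difference 0.145; significance level 0.05 (two-sided assumed, as sidedness is not stated); power 80%; 65 per group; 10% loss; 145 in total.

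**The plan's own figures.** The total reproduces: 130 / (1 − 0.10) = 144.4, rounded up to 145. The 65 per group cannot be checked independently because no SD is given, so I solved for it:

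- Normal approximation: SD = 0.145 / [(1.960 + 0.842) × √(2/65)] = 0.145 / 0.4915 = 0.295.
- Two-sample t-test: SD = 0.293, used below.

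**Assumptions not in the article:** no treatment effect; the same mean EQ-5D gain in both arms (0.05 to 0.10); correlation r between baseline and week 11 of 0.3 to 0.7; independent participants.

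**Formulas.** SD of change = 0.293 × √(2(1 − r)). Standard error = SD of change / √65. The probability p of a significant improvement within an arm comes from the noncentral t distribution with 64 degrees of freedom, noncentrality gain / standard error and critical value 1.998. The probability that the intervention arm is significant and the control arm is not is p(1 − p).

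| r | SD of change | Standard error | Gain 0.05: p | Gain 0.05: p(1 − p) | Gain 0.10: p | Gain 0.10: p(1 − p) |
|---|---|---|---|---|---|---|
| 0.3 | 0.347 | 0.0430 | 21% | 16% | 63% | 23% |
| 0.5 | 0.293 | 0.0363 | 27% | 20% | 77% | 17.5% |
| 0.7 | 0.227 | 0.0281 | 42% | 24% | 94% | 6% |

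An intermediate case, gain 0.07 and r = 0.5: noncentrality 0.07 / 0.0363 = 1.93, p = 48%, p(1 − p) = 25%. That is the ceiling, since p(1 − p) cannot exceed 0.25. The ranges are therefore 21% to 94% for the within-arm test and about 6% to 25% for significance in the intervention arm only.

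For reference, with no shared change p is 2.5% and p(1 − p) is 2.4%. With a shared decline of 0.05, a significant within-arm improvement occurs in 0.1% of trials or fewer.

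**Between-arm test.** A shared gain cancels in the difference (gain − gain = 0). Simulation with independent participants keeps the rejection rate at about 5% for every gain examined.

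**Test validity.** Mann-Whitney U applied to paired data with no change (65 people, simulated) rejects in about 2% of samples at r = 0.3 and about 0.1% at r = 0.7, against a nominal 5%. Ignoring the pairing thus makes the test strongly conservative. This needs no assumption about recovery.

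**The case against.** The best defence is that the between-arm comparison is already planned. It stands in the same sentence, the outcome section repeats it, and the sample size is built on it. A reader might infer that efficacy will be claimed from within-arm change, or from significance in one arm only. Nothing in the article says so; the misreading is a risk and not the stated basis for a conclusion. That part of the defence stands.

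Two further inferences are tempting and also go beyond the text:

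- **That participants enter at a temporary low and will recover.** Weight loss and acute disease can resolve, but eating dependency and chewing or swallowing problems also count toward the score and may persist. Selection is on EVS and not on EQ-5D, so regression to the mean in the primary outcome depends on a correlation that is not given.
- **That training just before baseline inflates the change.** The article says only that training precedes the intervention and gives no interval to t = 0. A training effect already present at t = 0 drops out of the change score; only continuing coordinator activity can contribute.

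The percentages depend on an assumed shared gain with no source in the article, and the 25% figure is a mathematical maximum. The pattern it describes is not a decision rule in the plan, so it is not directly comparable with a nominal error rate.

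On the test names, a condensed article can leave paired variants to a fuller document, and Mann-Whitney U on change scores between arms is legitimate. But the sentence assigns the listed tests to within-group comparisons too, and for that use two of the three are unsuitable as named.

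**Conclusion.** The point holds in a limited form. The plan states within-arm significance tests, gives them no role, and lists two tests that do not fit paired data. Within-arm change cannot separate the support from natural course or from coordinators shared by both arms.

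Under the assumed shared gain of 0.05 to 0.10, the intervention arm's own paired t-test would be significant in 21% to 94% of trials with no treatment effect, and significance in that arm alone would occur in about 6% to 25%. Both ranges rest on the back-solved SD of 0.293, correlations of 0.3 to 0.7 and 65 independent participants per arm. They illustrate how far a within-arm p-value can mislead; they do not predict this trial.

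The article does not show that natural recovery will occur, nor that within-arm results will decide the conclusion.

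**What to change.** In the Statistical analysis section, delete the words *within and*. Add that efficacy conclusions rest only on the between-arm difference in change. Report each arm's change descriptively, as an estimate with a confidence interval and no p-value, with a note that it includes natural course and coordinator activity.

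This is a wording change that needs no extra data, visits or participants. The only loss is the within-arm p-values. It also removes the mismatch between the named tests and paired data. It does not make the remaining between-arm tests account for the six clusters, which must be dealt with separately.
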